## Abstract

Prolonged periods of sitting at work can increase trunk muscle fatigue from the continuous contraction of deep trunk muscles. Insufficient activity of these muscles can decrease muscular support to the spine and increases stress on its passive structures. This can lead to reduced spinal mobility and impaired postural stability. It may also stimulate nociceptor activity leading to pain. However, frequently used recovery modalities such as muscle strengthening and stretching exercises, can be time-consuming, impractical, and difficult to implement in the workplace. Diaphragmatic breathing exercises, which increase the activity of the deep trunk muscles by raising intra-abdominal pressure, seem to be a suitable alternative. However, little is known as to what extent diaphragmatic breathing exercises contribute to the reduction of fatigue induced by prolonged sitting. This paper presents a study protocol that aims to investigate the acute effect of diaphragmatic breathing exercises on recovery of fatigue-induced changes in spinal mobility and postural stability in sedentary middle-aged adults at risk of developing non-specific low back pain. Twenty sedentary adults aged between 25 and 44 years will perform Abt’s fatigue protocol, followed by 1) active recovery using diaphragmatic breathing exercises and 2) passive recovery in the form of lying on the bed, respectively. There will be 1 week of rest in-between. Pre-fatigue, post-fatigue, and after the active and passive recovery, spinal mobility and postural stability will be evaluated using the spinal mouse device and a posturography system, respectively. The electromyography will be used to determine the muscle-fatigue conditions. We hypothesize that active recovery in a form of diaphragmatic breathing exercises would be more effective in restoring spinal mobility and postural stability followed by the fatigue of back and hamstring muscles compared to passive recovery in sedentary adults. Increasing core and respiratory muscle strength via these exercises could be beneficial for overall mobility and stability of the spine. Reducing compressive stress on the passive structures of the spine may be also beneficial for lowering low back pain. Therefore, we believe that diaphragmatic breathing exercises have the possibility to be incorporated into the workplace and contribute to better back health in sedentary middle-aged adults.

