## 2 Materials and methods

### 2.1 Study design

This experimental pre-post study is designed to investigate the acute effect of diaphragmatic breathing exercises on recovery of fatigue-induced changes in spinal mobility and postural stability in sedentary middle-aged adults at risk of developing non-specific low back pain. This is a study protocol that will be carried out and reported in accordance with the Standard Protocol Items: Recommendations for Interventional Trials statement (SPIRIT). Figure 1 illustrates the study design. The study has been approved by the ethics committee of the Faculty of Physical Education and Sport, Comenius University in Bratislava (No. 5/2022) and the Ethics Committee of Kerman University of Medical Sciences (IR.KMU.REC.1401.386). It also has been approved by Iranian Registry of Clinical Trials (registration reference: IRCT20221126056606N1).

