#### 2.3.2 Data collection

Data from all participants will be collected under three conditions:1. Pre-fatigue assessment (at baseline),2. Post-fatigue assessment (immediately after fatigue protocol),3. Post-recovery modalities assessment (immediately, and 15-min after cessation of active and passive modality, respectively).

Assessing the effects of the intervention at the 15-min follow-up can provide insight into the potential duration of these effects.

All participants will be tested at the same time of day by the same examiners.

The study will involve gathering individual demographic information and outcome data. The study team will enter the questionnaire data into a database and verify its accuracy before using it. All information and outcome data will be kept on password-protected computers that only the authorized members of the study team will be able to access. Data management will outline the procedures for gathering, recording, storing, and archiving data.

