### 2.4 Statistical analysis

Statistical analyses will be carried out using SPSS Statistics (SPSS Statistics Version 24; IBM Corporation^©^, United States). Prior to statistical comparisons, a Shapiro-Wilk test of normality will be performed for all variables. Not normally distributed data will be analyzed using nonparametric tests. Friedman’s test followed by Dunn’s *post hoc* test will be used for the comparison of the spinal mobility, postural stability and EMG variables at different assessment times (at baseline, immediately after Abt’s fatigue protocol, immediately after recovery modalities, 15-min after recovery modalities, 30-min after recovery modalities). The Kruskal–Walli’s test will be used for the inter-group comparisons (experimental group A vs. experimental group B) at each assessment. For the normally distributed data, a repeated measures Analysis of Variance (ANOVA) will be performed. Repeated measures ANOVA will be used to confirm if there are differences in each group (within-group comparisons), considering each group in isolation, between the five assessments in each of the spinal mobility variables (at baseline, immediately after Abt’s fatigue protocol, immediately after recovery modalities, 15-min after recovery modalities, 30-min after recovery modalities). To calculate between-group differences from baseline assessment to final follow up, a five-way repeated-measures ANOVA will be performed. With the spinal mobility and/or postural stability and/or EMG variables outcome as dependent factor, with five levels corresponding to every time of assessment (t1, t2, t3, t4, and t5), and the two groups (experimental group A vs. experimental group B) as independent factors. The Bonferroni correction will be applied to control for the increased probability of significant findings due to multiple testing. Between- and within-group effect sizes for all quantitative variables will be measured with the Cohen d coefficient: small effect (less than d = 0.2 and ηp2 = 0.01); moderate effect (approximately d = 0.5 and ηp2 = 0.06); and large effect (greater than d = 0.8 and ηp2 = 0.14) (Cohen, 2013). The α-level will be set to 0.05 for all statistical tests.

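### Section 2.4 names no active-versus-passive contrast of change from post-fatigue to post-recovery, although that change is what the trial sets out to compare

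*Protocol article*

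**What the plan says.** Section 2.1 gives the aim as "the acute effect of diaphragmatic breathing exercises on recovery of fatigue-induced changes in spinal mobility and postural stability". The Abstract makes it comparative: active recovery "would be more effective in restoring spinal mobility and postural stability followed by the fatigue of back and hamstring muscles compared to passive recovery". The same adults undergo both modalities one week apart, "followed by 1) active recovery using diaphragmatic breathing exercises and 2) passive recovery in the form of lying on the bed, respectively".

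Section 2.3.2 places two assessments before the modality in each session: one before the fatigue protocol (t1) and one immediately after it (t2). The post-recovery assessments follow.

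For normally distributed variables, section 2.4 plans two analyses:
- a repeated-measures ANOVA to "confirm if there are differences in each group (within-group comparisons), considering each group in isolation";
- for the modalities against each other: "To calculate between-group differences from baseline assessment to final follow up, a five-way repeated-measures ANOVA will be performed". This model has five time levels, t1 to t5, and two groups.

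For other variables it plans Friedman tests over time and a Kruskal-Wallis test between the two groups at each assessment. It names no between-modality contrast of change from t2 to a later time, and it uses neither t1 nor t2 as a covariate.

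**The concern.** The modality is applied after t2, so it can only affect t3 onward. A test of the hypothesis has to start from how fatigued each session left the person and ask how far each modality brought that person back. Section 2.4 does not fix such a test. Its wording points to the span from baseline, which mixes the depth of fatigue reached in a session with the recovery from it. Its omnibus ANOVA treats the two pre-modality times as outcome levels, so a significant interaction need not mean that recovery differed. The separate within-modality analyses compare nothing between modalities. In the non-normal branch, no planned test concerns change between modalities.

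At stake is the interpretation of the main result. A positive finding could reflect unequal fatigue between visits, and a short-lived benefit could be missed.

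**Working it through.** **The plan's own figure.** Section 2.2.2 gives a total of 11 for a within-between interaction (f = 0.25, alpha 0.05, power 0.80), without the number of groups, measurements or the correlation. With two groups and five times, λ = f²·N·m/(1 − ρ). At N = 11 this is 0.0625 × 11 × 5 / 0.5 = 6.9 for ρ = 0.5 (power 0.47) and 0.0625 × 11 × 5 / 0.25 = 13.75 for ρ = 0.75 (power 0.805). The figure can be neither confirmed nor refuted, and this point does not rest on it. It does show that an interaction was in mind.

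**Inputs for the check.** From the protocol: 20 participants, both modalities in each, five times (section 2.4), two-sided alpha 0.05. Assumed: SD 1 at each time; correlation ρ within a visit of 0.5, 0.7 or 0.8; correlation ρ − 0.2 between visits.

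**Precision of a two-time contrast.** Let D_j be active minus passive at time j.
- Var(D_j) = 2[1 − (ρ − 0.2)]
- Cov(D_j, D_k) = 2[ρ − (ρ − 0.2)] = 0.4
- Var(D_j − D_k) = 4[1 − (ρ − 0.2)] − 2 × 0.4 = 4(1 − ρ)
- SE with n = 20: √[4(1 − ρ)/20] = 0.316, 0.245, 0.200

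The SE is the same for t5 − t1 and t3 − t2. They differ only in what they estimate.

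**Case A: effect of 0.5 SD at t3 only.** The mean of D5 − D1 is 0, so its power equals alpha. The mean of D3 − D2 is 0.5, so the standardised effects are 0.5/0.316 = 1.58, 0.5/0.245 = 2.04 and 0.5/0.200 = 2.50.

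**Case B: no modality effect, but fatigue 0.3 SD deeper at one visit from t2 onward.** The mean of D5 − D1 is 0.3, giving 0.95, 1.22 and 1.50. The mean of D3 − D2 is 0.

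Simulated rejection rates (4,000 trials each, ρ = 0.5 / 0.7 / 0.8):

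| Scenario | Five-level interaction | t5 − t1 | t3 − t2 | t3 adjusted for t1, t2 |
|---|---|---|---|---|
| No difference at all | 0.05 / 0.05 / 0.04 | 0.05 / 0.04 / 0.05 | 0.05 / 0.05 / 0.05 | 0.05 / 0.05 / 0.05 |
| A: 0.5 SD at t3 only | 0.30 / 0.49 / 0.68 | 0.05 / 0.06 / 0.05 | 0.32 / 0.50 / 0.66 | 0.43 / 0.63 / 0.76 |
| B: 0.3 SD deeper fatigue, no effect | 0.14 / 0.19 / 0.28 | 0.15 / 0.21 / 0.29 | 0.05 / 0.05 / 0.05 | 0.13 / 0.15 / 0.18 |
| 0.5 SD at t3, t4 and t5 | 0.44 / 0.70 / 0.87 | 0.31 / 0.50 / 0.65 | 0.32 / 0.49 / 0.65 | 0.43 / 0.62 / 0.77 |

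The interaction here is computed within participants. In case B, adjusting the mean of the post-recovery times for t1 and t2 is worse than adjusting t3 alone: false rejection was 24% to 34% under the assumptions tried.

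**Where a power gain comes from.** For a sustained 0.5 SD effect and assumed person/session/residual variance shares of 0.59/0.10/0.30 and 0.40/0.10/0.50, the power of the five-level interaction is 0.69 and 0.45. The post-recovery mean has 0.92 and 0.82 unadjusted, and 0.95 and 0.81 adjusted. The gain comes from a one-degree-of-freedom averaged contrast, because the person effect already cancels in a crossover.

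**Non-normal branch.** Kruskal-Wallis at t3 compares 20 values with 20 values as if from 40 people. For the mean difference, the true variance is 1 − (ρ − 0.2) times what independence implies: 0.7, 0.5 and 0.4. The test is therefore too conservative. With no effect, it rejected in 0.2% to 1.7% of simulated trials under the assumed variances. It also compares levels at one time and ignores t1 and t2.

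**The case against.** The plan does compare the modalities. The sentence after "To calculate between-group differences from baseline assessment to final follow up, a five-way repeated-measures ANOVA will be performed" specifies both groups and all five times, so t2 and the post-recovery times are in the model and a modality-by-time interaction is available. The phrase about baseline and final follow-up may describe only the time span covered, and the sample-size section refers to an interaction. All of this stands. A reader might infer that the plan tests change from baseline in place of comparing recovery; the text does not go that far.

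Three other strong readings also fail:
- That chance differences at t1 or t2 inflate the error rate. They do not: the interaction rejects in 4% to 5% of trials when nothing differs. Trouble needs a systematic difference in fatigue depth between visits.
- That the non-normal branch has no between-modality test. Kruskal-Wallis does compare the modalities after recovery. It lacks pairing and a test of change.
- That covariate adjustment is the remedy and brings a large gain in power. Most of the gain comes from averaging, adjustment adds little unless session-to-session variance is large, and adjustment does not fully remove unequal fatigue depth.

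For a sustained effect, the five-level interaction does at least as well as t3 adjusted for t1 and t2 (0.44/0.70/0.87 against 0.43/0.62/0.77). The case against it is lack of specificity, not a general loss of power.

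**Conclusion.** The point holds in a limited form. The hypothesis, "We hypothesize that active recovery in a form of diaphragmatic breathing exercises would be more effective in restoring spinal mobility and postural stability", concerns change after fatigue, and section 2.4 fixes no between-modality contrast of that change. The interaction in its ANOVA is a valid 5% test of whether the two profiles differ in any way. It does not isolate recovery: a persistent 0.3 SD difference in fatigue depth alone makes it significant in 14% to 28% of trials. If the baseline-to-last contrast is what is meant, it has about 5% power for an effect gone by the last assessment, against 32% to 66% for t3 − t2. Section 2.3.2 treats the duration of effect as something still to be learned, so fading is a realistic case. For non-normal variables, the planned test is unpaired and does not address change.

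The sizes rest on assumed correlations, variances and effect patterns; the protocol gives none. The 5% rate for change from t2 also assumes that the deeper fatigue carries through unchanged. If people who are more fatigued naturally regain more, the change score would be affected too. This is a reason to report two estimates side by side. The defect is repairable and should be corrected before analysis.

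**What to change.** Rewrite section 2.4 as follows.

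1. **Primary comparison.** Use the within-participant active-minus-passive difference in change from same-session post-fatigue (t2) to post-recovery, with a 95% CI. State in advance whether post-recovery means the immediate assessment or an average of the later ones. The first suits a brief effect, the second a lasting one.
2. **Reported beside it.** Give the post-recovery difference adjusted for same-session t1 and t2, with participant as a random effect. Add a note that adjustment does not fully remove a systematic difference in fatigue depth.
3. **Period.** Include a period term only if the order of modalities varies. The Abstract reads as a fixed order, and then period and modality cannot be separated.
4. **Non-normal variables.** Analyse the same change contrast on a log scale or with a paired test (signed-rank or permutation), in place of Kruskal-Wallis.
5. **Within-modality analyses.** Label them descriptive.

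No new data are needed. The cost is the rewording and a little more analysis work. The downside is that the change contrast can have less power than the adjusted post-recovery mean; at t3 in case A it has 0.32 to 0.66, against 0.43 to 0.76 with adjustment.

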## 3 Discussion

The present study will address the modeling of trunk muscle fatigue and recovery-related changes in spinal mobility and postural stability in sedentary middle-aged adults at risk of developing non-specific low back pain. People who spend most of their working hours seated, due to their work nature, are more susceptible to developing musculoskeletal disorders (Hanna et al., 2019). Low back pain is the most prevalent occupational musculoskeletal disorder (Csuhai et al., 2020; Zemková et al., 2021c). During prolonged sitting, the static loading of the lumbar spine can cause deep trunk muscles fatigue that may arise from continuous contraction of the muscles (Areeudomwong et al., 2012). Consequently, the neural control subsystem attempts to maintain spinal stability by increasing superficial trunk muscles activation in order to compensate for deep trunk muscles dysfunction (Saiklang et al., 2022). Under fatigue, there is an increased activity of superficial trunk muscles which can reduce the muscular support to the spine and increase stress on ligaments and intervertebral discs. Consequently, it reduces intervertebral disc height, leading to impaired spinal mobility. The reduction of disc height increases the amount of compression on sensitive spinal structures. This may stimulate nociceptor activity, which could be one of the reason for developing pain (Saiklang et al., 2022).

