In addition to decrease trunk muscle activity under fatigue, proprioceptive sensitivity also decreases by muscle fatigue (Tajali et al., 2022). The combination of these two factors, can lead to impairment of postural stability (Larson and Brown, 2018). Adverse effect of trunk muscle fatigue on ability of maintain balance can be explained by alternation of neurophysiological mechanisms. Repeated muscular contractions caused by mechanical constraints reduce the activity of muscle spindles (Macefield et al., 1991). Motoneurons activation also reduces under fatigue, which results in decreasing of the discharge frequency of sensorial fibers in muscle spindles (Madigan et al., 2006). Thus, the integration of sensory inputs and the firing patterns of motoneurons are influenced, which leads to fewer motor units being recruited to control postural sway (Gribble and Hertel, 2004). Additionally, the central nervous system does not get accurate information about body location in space at any moment due to variations in proprioceptive input brought on by weariness (Martin et al., 2006). Under fatigue, inputs from group III and IV muscle afferents from antagonist or homonymous muscles decrease extensor motor neurons, whilst flexor motor neurons innervations are facilitated (Martin et al., 2006). Especially the fatigue of lumbar extensor muscles decreases the joint movement sense (Taimela et al., 1999), which initially increases larger lumbar motions and subsequently also postural sways (Pline et al., 2005).

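### The between-modality tests in section 2.4 are not anchored on the pre-fatigue value, so a significant difference need not mean better restoration

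*Protocol article*

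**What the plan says.** The Abstract states the hypothesis that active recovery "would be more effective in restoring spinal mobility and postural stability" than passive recovery. The same 20 people undergo both modalities, one week apart.

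Section 2.4 sets out three pieces of analysis that matter here:

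- **Between modalities, normal data.** "To calculate between-group differences from baseline assessment to final follow up, a five-way repeated-measures ANOVA will be performed". The model is then specified: "With the spinal mobility and/or postural stability and/or EMG variables outcome as dependent factor, with five levels corresponding to every time of assessment", with the two groups as the other factor. The text calls it five-way, but it describes one five-level time factor and one two-level group factor. I read it as a 5 × 2 group-by-time analysis, with groups A and B standing for the two modalities.
- **Between modalities, non-normal data.** A Kruskal-Wallis test compares the groups at each assessment.
- **Within each group.** "Repeated measures ANOVA will be used to confirm if there are differences in each group (within-group comparisons), considering each group in isolation". Friedman's test with Dunn's post hoc test is the nonparametric counterpart and covers mobility, stability and EMG. Baseline and post-fatigue are two of the five times.

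For fatigue itself, the Abstract says: "The electromyography will be used to determine the muscle-fatigue conditions". Section 2.3.2.2.1 gives the EMG signs of fatigue and of recovery. Section 2.3.3 ends the circuit on loss of form or tempo and on a Borg rating of at least 17.

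**The concern.** Restoration means return towards the pre-fatigue state. To support that claim, a comparison between modalities has to refer to that state. Neither planned comparison does so.

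- The group-by-time test is an omnibus test with no direction. It also spends part of its degrees of freedom on the post-fatigue time, which precedes the start of either modality.
- The Kruskal-Wallis test looks at one time point and ignores both baseline and post-fatigue values.

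If fatigue reduces an outcome as predicted, the modality with the higher post-recovery value is also the one closer to baseline, provided it does not overshoot. If the circuit leaves the outcome unchanged or raises it, the higher value is an acute effect or a persisting deviation.

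The procedures make this plausible for range of motion. Under section 2.3.2.2.2 the Spinal Mouse test is done without warm-up. Under section 2.3.3 a 10-minute warm-up, 5 minutes of it stretching aimed at the hamstrings and trunk, and then four cycles of trunk exercise come between the baseline and post-fatigue tests. At stake is whether a significant difference in flexion range can be reported as better recovery.

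**Working it through.** The plan gives no figure of its own on this point. The sample-size result in section 2.2.2 does not bear on it, apart from supplying n of about 20 and alpha 0.05.

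**Step 1: arithmetic on an assumed scale.** Values are means at baseline / post-fatigue / after active / after passive. Raw difference = active − passive. Distance = |post-recovery − baseline|.

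| Case | Values | Raw difference | Distance, active | Distance, passive |
|---|---|---|---|---|
| (a) fatigue lowers | 100 / 92 / 98 / 94 | +4 | 2 | 6 |
| (b) no fatigue effect | 100 / 100 / 106 / 101 | +5 | 6 | 1 |
| (c) fatigue raises | 100 / 106 / 109 / 102 | +7 | 9 | 2 |

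The raw difference favours active in all three cases. Only in (a) is active nearer to baseline.

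**Step 2: why the planned interaction cannot separate the cases.** Three sets of means over t1 to t5, with an assumed shift of 8 units:

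- Fatigue lowers: active 100, 92, 100, 100, 100; passive 100, 92, 92, 92, 92.
- No fatigue effect: active 100, 100, 108, 108, 108; passive 100 throughout.
- Fatigue raises: active 100, 108, 108, 108, 108; passive 100, 108, 100, 100, 100.

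Active minus passive is 0, 0, 8, 8, 8 in every case. A group-by-time interaction depends on the means only through this difference profile, so its power is the same in all three.

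**Step 3: size at n = 20.** Assumed SD 15 and within-person correlation 0.8, both modalities in the same people, tests at 0.05 without Bonferroni correction.

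- SD of a paired difference at one time = 15 × √(2 × (1 − 0.8)) = 9.49. The standardised difference at t3 = 8 / 9.49 = 0.84, and paired-test power is about 95%.
- Interaction: the difference profile has mean 4.8 and centred sum of squares 2 × 4.8² + 3 × 3.2² = 76.8. The noncentrality is 20 × 76.8 / 90 = 17.1 on 4 and 76 df, and power is about 91%.

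A simulation of 10,000 trials per case agrees:

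| Case | Interaction significant | t3 significantly favours active | Both, and active further from baseline |
|---|---|---|---|
| Fatigue lowers | 92% | 95% | 0.4% |
| No fatigue effect | 91% | 95% | 86% |
| Fatigue raises | 92% | 95% | 87% |

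The paired tests use the pairing that the design offers. They stand in for the plan's between-group tests and do not replicate them.

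**Step 4: what does separate the cases.** With equal baselines, the difference between modalities in signed change from baseline equals the raw difference (+4, +5, +7 in step 1). Anchoring therefore removes baseline differences between visits, but that one number is not enough. The separation comes from each modality's remaining deviation, read against the fatigue effect:

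- (a) −2 and −6 after a fatigue effect of −8
- (b) +6 and +1 after 0
- (c) +9 and +2 after +6

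**The case against.** The strongest reply is that section 2.4 already holds the needed information. Baseline and post-fatigue are levels of the time factor, within-group tests cover all five assessments with a Bonferroni correction, and the between-group model is meant to run from baseline to final follow-up. In cases like (b) and (c) the within-group results would show the wrong direction. This stands, and it rules out the stronger reading that the plan never asks whether the circuit moved an outcome. What remains is that no between-modality conclusion depends on those results and that the Kruskal-Wallis comparison does not use them.

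A reader might also infer that the article predicts both directions for spinal motion. It does say that extensor fatigue impairs movement sense, "which initially increases larger lumbar motions and subsequently also postural sways", but that sentence explains loss of balance and does not concern maximal range by Spinal Mouse. For mobility, the Introduction and the Discussion predict a decrease: "Consequently, it reduces intervertebral disc height, leading to impaired spinal mobility".

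Nor is fatigue confirmed by the Borg rating alone. Form and tempo criteria apply, and the EMG variables are to be evaluated for fatigue and recovery and are tested over time.

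Finally, a condensed article may leave contrasts to a fuller document. That would excuse silence, but here the between-modality tests are stated, and as stated they do not match the hypothesis.

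**Conclusion.** The point holds as a mismatch between the claim and the test. The hypothesis concerns restoration, while the stated between-modality tests respond to any difference between the modalities, whatever fatigue did to the outcome. That follows from the difference profile alone and needs no numerical assumption.

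The size is conditional. The 0.4%, 86% and 87% rest on an assumed SD, correlation and 8-unit shift, on unadjusted paired tests, and on my reading of the ANOVA as group by time. They illustrate the problem and do not forecast this trial. The documents do not show that fatigue will leave range of motion unchanged or increase it, so they do not support saying that the result will carry the wrong sign. The unheated baseline and the stretching before the post-fatigue test make that case plausible enough to plan for. The change should be made, and it is inexpensive.

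**What to change.** Amend section 2.4 as follows:

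1. Make the between-modality comparison a within-person contrast of the post-recovery value relative to the same-visit pre-fatigue value (remaining deviation), at each post-recovery time. Use it in both the parametric and the nonparametric branch. Report the remaining deviation for each modality as well as the difference.
2. State the direction of benefit for each outcome in advance. For mobility, take the decrease under fatigue that the Introduction and Discussion predict as the deficit to be recovered.
3. Beside each contrast, report the estimated baseline to post-fatigue change with its confidence interval, pooled over both visits, and use EMG median frequency as the muscle-fatigue check.
4. Where that change is absent or opposite to the predicted direction, describe a modality difference as an acute effect and not as restoration.

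Do not sign the outcome by the observed direction of the fatigue effect, because about 20 people are too few to let the data set the direction of benefit. Do not make the comparison conditional on a significant fatigue effect either, since non-significance at this size does not show absence. Judge item 4 from the estimate and its interval.

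The cost is plan wording and a few contrasts on measurements already scheduled. The downside is that some outcomes may no longer support a recovery claim.
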